## Abstract

**Aims:**

The BioBone consortium aims to validate circulating CD8 + TEMRA cells as a prognostic biomarker for predicting impaired fracture healing outcomes in a prospective, blinded, multicenter clinical study. The primary performance parameters are the pre-operative identification of at least 30% of patients who ultimately experience impaired healing at the first clinical endpoint, with a specificity greater than 90% to minimize the false-positive rate.

**Methods:**

BioBone is a prospective, blinded, multicenter biomarker validation study designed to assess the prognostic value of circulating CD8 + TEMRA cells in fracture healing. A total of 640 patients aged 18 to 80 years with fractures of the humeral diaphysis, radial and/or ulnar diaphysis, femoral neck, trochanteric femur, femoral diaphysis, distal femur, proximal tibia, tibial diaphysis and distal tibia will be enrolled. The study is powered to validate the target assay performance and accounting for 6–7 potential confounders at an expected incidence of 10% impaired healing. Biomarker levels will be measured pre- and post-operatively using flow cytometry (FC) and patients will be monitored for one year. The primary endpoint is fracture healing status at 17–19 weeks (normal healing or delayed healing), while the secondary endpoint evaluates healing at nine months (delayed healing or pseudarthrosis). Fracture consolidation will be assessed through radiographs or computed tomography (CT) scans in conjunction with clinical assessments such as range of motion and weight-bearing capacity. Key outcome measures include radiographic analysis (RUST/RUSH scores), functional and patient-reported outcomes (e.g. weight bearing ability, range of motion, and the SF-36 questionnaire), as well as socioeconomic parameters (e.g. work capacity, rehabilitation needs, mobility). The predictive performance (sensitivity, specificity, NPV, PPV) of the biomarker will be determined in a prospective, double-blinded analysis, where CD8 + TEMRA blood levels are measured prior to surgical treatment and healing status at clinical endpoints is assessed by independent observers. Additional immunological examination and in vitro analysis of blood and fracture hematoma samples will further investigate the mechanism of action of CD8 + TEMRA cells in impaired human bone regeneration.

**Conclusion:**

The BioBone study will validate the suitability of CD8 + TEMRA cells as a prognostic marker for impaired fracture healing and their integration into routine clinical practice. The results could have a global impact by incorporating immune-based prognostic tools into clinical workflows, paving the way for precision medicine approaches in trauma care. The BioBone study is funded by the German Federal Ministry of Education and Research (BMBF).

## Introduction

In 2019, 178 million bone fractures were reported worldwide, most commonly humeral, radial, tibial and femoral fractures [1]. Although bone has a very high endogenous regenerative potential, the prevalence of non-union or delayed fracture healing ranges between 5 and 15% in industrialized nations [2–4]. These patients require additional surgical interventions (median of 2 revision procedures [5–7], leading to prolonged hospitalization and rehabilitation periods (median time = 23 months [7]. Health economic analyses suggest that in-patient costs alone range from 18,000–25,000€ per compromised healing case, although this varies depending on the localization of the fracture, the type of treatment, and the country-specific health care system [8]. When out-patient treatment and productivity losses are included, total costs increase to 36,800–50,000€ per case, underscoring the socioeconomic challenge [9, 10].

Currently there are no reliable prognostic methods for early prediction of patients at risk of compromised fracture healing outcomes [11–13]. Hence, there is a clear medical demand for novel approaches enabling early patient stratification to guide therapeutic strategies and improve bone healing. Such strategies include advanced surgical interventions [14, 15], tailored rehabilitation programs or fixation devices, which are currently only applied in revision surgery. Early prediction of the risk for compromised healing would not only reduce the financial burden associated with prolonged care and lost productivity, but also improve the quality of life of affected patients through timely and personalized interventions [12, 16–18].

Recent evidence highlights the critical role of adaptive immunity in bone repair, with T cells modulating healing even in the absence of infection [19–22]. Delayed fracture healing correlates with increased levels of CD8 + terminally differentiated effector memory T cells (CD8 + TEMRA) [23–25]. This difference is long-lasting and reflects an individual immune profile rather than an acute immune response to injury. The frequency of CD8 + (CD3 + CD8 + CD28-CD57 +) TEMRA cells is determined by lifelong antigen exposure and correlates with the overall immune experience. Furthermore, they proliferate poorly but have potent effector functions such as cytotoxicity and cytokine release. CD8 + TEMRA cells can be directly activated by stress signals or pro-inflammatory cytokines without antigen presentation. These cells are enriched in the fracture hematoma where they act as major producers of pro-inflammatory cytokines such as interferon-γ and tumor necrosis factor-α [26]. This disrupts the resolution of the initial inflammatory healing phase, impairs pro-osteogenic cell function and inhibits osteogenesis. In animal studies, adoptive (systemic) transfer of CD8 + T cells completely impaired bone healing, whereas antibody-mediated depletion of circulating CD8 + T cells significantly enhanced endogenous fracture repair. These findings highlight the prognostic potential of CD8 + TEMRA cell quantification for predicting fracture healing outcomes and could assist to adapt the treatment strategy [23, 27, 28].

### Aims and Objectives

The aim is to conduct a prospective, blinded clinical validation study of the CD8 + TEMRA cells as a prognostic biomarker to predict healing outcome after fracture. Aimed test characteristics are a positive predictive value (PPV) > 60% and a specificity > 90%, as well as the clinical routine suitability or cost-effectiveness. We hypothesize that:

The perioperative cut-off level of CD8 + TEMRA cells (> 38%) is a prognostic marker with a high diagnostic accuracy to distinguish between patients with normal-, delayed or incomplete (non-union) fracture healing.Poor bone fracture healing can be predicted with a very high specificity (> 90%) prior to surgical intervention, allowing a more personalized treatment to improve the outcome with high cost effectiveness.As the biomarker reflects the pathogenic impact of TEMRA cells on fracture healing, precise identification of poor healers would offer novel immune-modulatory approaches to improve poor healing.

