#### Sample size calculation

A total number of 640 patients must be completely analyzed. This number is required to simultaneously construct a 97.5%-confidence interval with half-length of 3% for an expected specificity of 90% and a 97.5%-confidence interval with a half-length of 10% for an expected sensitivity of 85% associated with the assumed cut-off and a prevalence of delayed fracture healing of approximately 10%. The 97.5%-confidence intervals are used to maintain a global alpha error of 5%. Assuming a consent rate of 70% among patients meeting all inclusion and exclusion criteria and a dropout rate of 20%, approximately 1,140 patients will need to be screened to enroll 800 participants and obtain 640 complete datasets for analysis. Sample size calculation was done as described by Krummenauer and Kauczor [29]. According to this sample size, we use Harrell's rule that 10 to 20 events per independent predictor variable are necessary to ensure a stable regression model. With the above sample size, approximately 6 predictor variables, respective covariables or confounders 640*0.1/10 can be entered in a final logistic regression model to discriminate regarding the fracture healing outcome [30].

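### The aimed PPV above 60% is not supported by the planning values, which imply a PPV of about 49%

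*Protocol article*

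**What the plan says.** Aims and Objectives sets two performance aims side by side: "Aimed test characteristics are a positive predictive value (PPV) > 60% and a specificity > 90" percent.

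The Sample size calculation gives the values on which the study is planned: a "97.5%-confidence interval with half-length of 3% for an expected specificity of 90" percent, a "97.5%-confidence interval with a half-length of 10% for an expected sensitivity of 85" percent, and "a prevalence of delayed fracture healing of approximately 10" percent. The Methods part of the Abstract repeats the last figure ("at an expected incidence of 10% impaired healing"). The Introduction gives a background range: "the prevalence of non-union or delayed fracture healing ranges between 5 and 15% in industrialized nations".

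The article states no expected PPV and does not link the PPV aim to these planning values. The Aims part of the Abstract names the primary performance parameters as a sensitivity of at least 30% and a specificity above 90%. It does not mention PPV there. Statistical analyses lists PPV among the accuracy measures to be reported with 95% confidence intervals.

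**The concern.** PPV is not a free quantity. Once sensitivity, specificity and prevalence are fixed, it follows by arithmetic. The plan fixes all three for its sample size and separately states a PPV aim, so the aim can be checked against the plan's own figures. At 10% prevalence there are nine normal healers for every impaired healer. A 10% false-positive rate among them yields about as many false positives as there are impaired healers in total.

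At stake is how the validation will be read. If the marker performs as planned, it meets the planned sensitivity, lies at the edge of the specificity aim and falls well short of the PPV aim. The article does not say which of these figures should then carry the conclusion.

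**Working it through.** **Inputs.** Sensitivity (Se) 85%, specificity (Sp) 90%, prevalence (p) 10%, two 97.5% intervals with half-lengths 10% and 3%, and N = 640, all from Sample size calculation. Prevalence range 5 to 15% from the Introduction. PPV aim above 60% and specificity aim above 90% from Aims and Objectives.

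**Step 1: reproduce the plan's 640.** Normal-approximation precision formula, n = z² × π(1 − π) / h², with z = 2.241 (two-sided 97.5%).

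- Sensitivity: 2.241² × 0.85 × 0.15 / 0.10² = 64.05 impaired healers; divided by 0.10, this is 640.5 patients.
- Specificity: 2.241² × 0.90 × 0.10 / 0.03² = 502.4 normal healers; divided by 0.90, this is 558.2 patients.

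The larger figure matches the stated 640. So 85%, 90% and 10% are the operative planning values, and sensitivity drives N.

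**Step 2: the PPV they imply.** PPV = Se·p / [Se·p + (1 − Sp)(1 − p)].

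- Planning values: 0.085 / (0.085 + 0.090) = 48.6%. Among 640 patients this is 0.85 × 64 = 54.4 true positives against 0.10 × 576 = 57.6 false positives.
- Ceiling at Se = 100%, Sp and p unchanged: 0.100 / (0.100 + 0.090) = 52.6%.

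**Step 3: the cited prevalence range, at Se 85% and Sp 90%.**

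| Prevalence | Calculation | PPV |
|---|---|---|
| 5% | 0.0425 / (0.0425 + 0.0950) | 30.9% |
| 10% | 0.0850 / (0.0850 + 0.0900) | 48.6% |
| 15% | 0.1275 / (0.1275 + 0.0850) | 60.0% |

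**Step 4: the specificity that the PPV aim needs.** Solving PPV = 60% for specificity gives Sp = 1 − Se·p × (0.4/0.6) / (1 − p).

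- Se 85%, p 10%: 1 − 0.085 × 0.6667 / 0.90 = 93.7%.
- Se 100%, p 10%: 1 − 0.100 × 0.6667 / 0.90 = 92.6%.

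**Step 5: chance of observing the aim if the planning values are true.** With 64 impaired and 576 normal healers, Se 85% and Sp 90%, the exact binomial probability that the observed PPV exceeds 60% is about 0.1%. If the true specificity were 93%, it would be about 26%; at 95%, about 90%.

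**The case against.** **Specificity above 90% is a floor.** A marker with a true specificity of 94% at 85% sensitivity would meet both aims. This stands: a reader might infer that the two aims contradict each other, and they do not. It does not remove the mismatch, because the sample size section expects 90%, not 94%. At 93%, the upper edge of the planned specificity interval, PPV at 85% sensitivity is 0.085 / (0.085 + 0.063) = 57.4%. Only with both measures at their upper edges (95% and 93%) does it pass, at 0.095 / (0.095 + 0.063) = 60.1%.

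**The article never states an expected PPV of 49%.** Correct. The figure is derived, and the 90% specificity enters the article only as an input for interval width. It is nevertheless the value at which the plan expects the marker to operate.

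**PPV is not a pass/fail criterion.** A reader might infer that a marker performing as planned would be declared a failure. The article does not support this. The Abstract's primary performance parameters are sensitivity and specificity, the alpha is split between those two, and there is no decision rule on PPV. What remains is a stated aim that the plan's own figures do not support.

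**Prevalence and cut-off are not fixed exactly.** Prevalence is given as approximate, and at 15% the implied PPV lies on the 60% line. Statistical analyses also provides for an optimised cut-off besides the predefined one above 38%, which may have a different sensitivity and specificity. Both points are fair, but no planning value is given for the optimised cut-off, and the line is only touched at the top of the cited range.

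**The Abstract's 30% sensitivity.** One could calculate a lower PPV from it. But it is a minimum, while the 85% is an expectation; their difference is a separate matter and is not used here.

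**Conclusion.** The concern holds in a limited form: the PPV aim is not supported by the values on which the study is planned. The shortfall is about 11 percentage points (48.6% against more than 60%), and at least 7 points whatever the sensitivity (ceiling 52.6%), given 90% specificity and 10% prevalence. At 85% sensitivity and 90% specificity, prevalence would have to exceed 15%, the top of the cited range.

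It follows that meeting the specificity aim does not ensure meeting the PPV aim. At 85% sensitivity and 10% prevalence, the PPV aim amounts to an unstated requirement of specificity above about 93.7%.

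The result rests on the article's own planning values, which reproduce its sample size. It affects neither that sample size nor the planned intervals. It needs correction because a published performance target disagrees with the plan's own figures.

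**What to change.** Before data are seen, make the aims agree with the planning values in one of two ways, and state that the PPV aim applies at 10% prevalence.

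1. **Restate the PPV aim** as the value that the planned accuracy implies: about 49% at 85% sensitivity, 90% specificity and 10% prevalence. This is a change of wording. The cost is one less favourable stated figure.
2. **Keep PPV above 60%** and raise both the specificity aim and the expected specificity in Sample size calculation to at least 94%. At 85% sensitivity and 10% prevalence this gives 0.085 / (0.085 + 0.054) = 61.2%. The cost is a stricter specificity aim, which the sponsor should be able to support for the predefined cut-off. The margin is small: if sensitivity were 75%, the lower edge of its planned interval, the required specificity would be 1 − 0.075 × 0.6667 / 0.90 = 94.4%.

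Which of the two fits the intended use is for the sponsor to decide. Neither needs more patients. Sensitivity drives the 640, and a 3% half-length at 94% specificity needs 2.241² × 0.94 × 0.06 / 0.03² = about 315 normal healers, or about 350 patients in total.

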## Methods

### Ethical considerations

The CD8 + TEMRA cells will be analyzed in EDTA blood samples of < 2 ml, which are usually taken in addition to routine blood collection at the admission of the patients for the surgery intervention. There is no additional risk for the patients and the study has no influence on standard care of the patients. The data are protected according to the regulatory rules and the participants’ confidentiality is guaranteed. The blood collection for the validation as well as the study procedures are already approved by the local institutional review board (IRB) of the Charité for the recruitment center Charité Universitätsmedizin Berlin, Unfallkrankenhaus Berlin, Vivantes Klinikum Spandau (IRB number: EA2/096/11), University Hospital Carl Gustav Carus (IRB number: 310072016), University Hospital Münster (IRB number: 2018–728-b-S), Friedrich-Schiller University, Jena (IRB number: 4689–02/16) and University Hospital Leipzig (IRB number: 299/18-lk).

#### Inclusion–exclusion criteria

The patients will be recruited at the following clinical recruitment centers: Charité Universitätsmedizin Berlin, Unfallkrankenhaus Berlin, Vivantes Klinikum Spandau, University Hospital Leipzig, Waldkliniken Eisenberg, University Hospital Münster and University Hospital Carl Gustav Carus Dresden.

Adhering to the following inclusion and exclusion criteria, we will perform a compatibility assessment and all eligible patients will be informed about the study content to receive their consent. Written consent will be obtained from each subject to be involved in the clinical study by using the IRB approved informed consent form prior to the conduct of any study-related activity. The subjects will also be instructed that their participation is voluntary and that they are free to withdraw their consent and to discontinue their participation at any time without prejudice (Table 1).

**Table 1 Tab1:** Inclusion–exclusion criteria

**Inclusion Criteria:** Subjects must meet all of the inclusion criteria listed below to be eligible for the study
1. Male or female subjects 2. Subjects 18—80 years of age at the time of screening 3. Only closed fractures 4. Fractures of the humeral diaphysis, radial and/or ulnar diaphysis, femur or tibia 5. Monotrauma or type of trauma with comparable post-surgery mobilization regime 6. Osteosynthesis 7. Signed informed consent form
**Exclusion Criteria:** Subjects with any one of the exclusion criteria listed below will not be eligible for the study
1. Cancer related fracture 2. Periprosthetic fracture 3. Additional long bone fracture with the exception of index fractures (inclusion criteria) 4. Additional thoracic trauma 5. Known active hepatitis B virus or hepatitis C virus infection at screening 6. Known human immunodeficiency virus (HIV) infection, severe uncontrolled inflammatory disease or severe uncontrolled autoimmune disease (e.g., ulcerative colitis, Crohn’s disease, etc.) 7. Active malignancy or history of malignancy within 5 years prior to screening 8. Known diagnosis of moderate to severe dementia based on subject’s medical history or severe psychiatric disorder 9. Known history of drug or alcohol abuse in the past 12 months, based on self-report or medical record 10. History of autologous/allogeneic bone marrow transplantation 11. Exposure to allogeneic cell-based therapy in the past or exposure to autologous cell therapy in the last 12 months before screening 12. Pregnancy 13. Subject is currently enrolled in an investigational device or drug trial, or has not yet completed a period of at least 30 days since ending other investigational device or drug trial(s) 14. Subject is detained or institutionalized under a court order or administrative order 15. In the opinion of the investigator, the subject is unsuitable for participating in the study (patient compliance)

#### Sample size calculation

A total number of 640 patients must be completely analyzed. This number is required to simultaneously construct a 97.5%-confidence interval with half-length of 3% for an expected specificity of 90% and a 97.5%-confidence interval with a half-length of 10% for an expected sensitivity of 85% associated with the assumed cut-off and a prevalence of delayed fracture healing of approximately 10%. The 97.5%-confidence intervals are used to maintain a global alpha error of 5%. Assuming a consent rate of 70% among patients meeting all inclusion and exclusion criteria and a dropout rate of 20%, approximately 1,140 patients will need to be screened to enroll 800 participants and obtain 640 complete datasets for analysis. Sample size calculation was done as described by Krummenauer and Kauczor [29]. According to this sample size, we use Harrell's rule that 10 to 20 events per independent predictor variable are necessary to ensure a stable regression model. With the above sample size, approximately 6 predictor variables, respective covariables or confounders 640*0.1/10 can be entered in a final logistic regression model to discriminate regarding the fracture healing outcome [30].

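### The abstract calls the study powered to validate its performance targets, but 640 is a precision calculation and its planning specificity of 90% is the very bound to be exceeded

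*Protocol article*

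**What the plan says.** **Targets and power claim.** In the protocol article, the abstract (Aims) sets two primary performance parameters: pre-operative "identification of at least 30% of patients who ultimately experience impaired healing at the first clinical endpoint", and specificity greater than 90%. The abstract (Methods) then says: "The study is powered to validate the target assay performance". The section Aims and Objectives repeats specificity above 90% and adds a positive predictive value (PPV) above 60%; it does not mention the 30%.

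**Sample size.** The section Sample size calculation says: "A total number of 640 patients must be completely analyzed". The number is to deliver two intervals at once: "a 97.5%-confidence interval with half-length of 3% for an expected specificity of 90" per cent, and "a 97.5%-confidence interval with a half-length of 10% for an expected sensitivity of 85% associated with the assumed cut-off". It assumes "a prevalence of delayed fracture healing of approximately 10" per cent. On error control it says: "The 97.5%-confidence intervals are used to maintain a global alpha error of 5" per cent. The section states no null or threshold value, no power and no rule for declaring a target met. It mentions neither the 30% sensitivity nor the 60% PPV.

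**The concern.** A reader of the abstract will take it that 640 patients give a known, high chance of showing the stated performance. The only calculation in the document answers a different question, namely how wide two intervals will be at assumed values.

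For specificity the gap matters. The value assumed for planning is the value that the biomarker is supposed to beat, so an interval centred where the plan expects it cannot exclude 90%.

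This is a validation study with a prespecified cut-off (above 38%). Without a rule, an observed specificity of, say, 91% could be reported as success or as failure.

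**Working it through.** **Inputs** (Sample size calculation): N = 640, prevalence 10%, hence 64 impaired and 576 normal healers; 97.5% two-sided intervals, z = 2.2414; planning sensitivity 85% and specificity 90%. Targets (abstract, Aims): sensitivity at least 30%, specificity above 90%.

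**1. Reproducing 640.** With n = z²p(1−p)/d²:
- Sensitivity: 2.2414² × 0.85 × 0.15 / 0.10² = 64.05 impaired; divided by 0.10 = 640.5.
- Specificity: 2.2414² × 0.90 × 0.10 / 0.03² = 502.4 normal; divided by 0.90 = 558.

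The larger is about 640, so the stated number reproduces and sensitivity drives it. Enrolment also follows: 640/0.8 = 800, and 800/0.7 = 1,143, stated as about 1,140.

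**2. Half-lengths at 640**, z·√(p(1−p)/n):
- Sensitivity 85%, n = 64: 10.0 points, as stated.
- Specificity 90%, n = 576: 2.8 points, within the stated 3.
- Sensitivity 30%, n = 64: 12.8 points. The plan makes no precision statement at this value.

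**3. Specificity against its target.** The expected interval is 90% ± 2.8 points, about 87.2% to 92.8%, which includes 90%. Assume, because the document gives no rule, that validation means a lower 97.5% limit above 90%. The smallest count that meets this is 533/576 (92.5%) with Wald limits and 535/576 (92.9%) with Clopper-Pearson limits. Exact binomial probabilities of reaching it:

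| True specificity | Clopper-Pearson | Wald |
|---|---|---|
| 90% | 1.0% | 2.2% |
| 92% | 24% | 35% |
| 93% | 59% | 70% |
| 93.5% | 76% | 85% |
| 94% | 89% | 94% |

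Wilson limits give the Clopper-Pearson column. If a point estimate above 90% were enough (at least 519/576), the probability would be about 50% at a true 90% and 96% at 92%.

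**4. Sensitivity against its floor.** On the same lower-limit rule, 29/64 (45%) is needed with Clopper-Pearson or Wald limits. The probability is practically 100% at a true 85%, 99% at 60%, 81% at 50% and 23% at 40%. With Wilson limits the last two are 87% and 31%.

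**5. PPV at 10% prevalence**, Se × 0.1 / (Se × 0.1 + (1 − Sp) × 0.9):
- 85%/90%: 0.085 / (0.085 + 0.090) = 48.6%.
- 30%/90%: 0.030 / (0.030 + 0.090) = 25.0%.

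Both are below the 60% aim. At sensitivity 85%, a PPV of 60% needs specificity of about 93.7%; at sensitivity 30%, about 97.8%.

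**The case against.** **The design is one of estimation.** Sizing for interval width is legitimate, the section openly describes it as such, and no figure in it is miscalculated. All of this stands. The criticism is of the abstract's word 'powered', and of a planning value placed on its own bound.

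**The success rule is supplied by the review.** This is correct. The document does not say that a lower limit must exceed 90%, and Aims and Objectives calls the figure an aim. The probabilities are therefore conditional on that rule, and they vary with the interval method. The conclusion about the claim does not depend on the rule: with a point-estimate rule, success at the planned specificity is a coin toss, and the section still contains no power calculation.

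**Sensitivity.** A reader might infer that planning at 85% contradicts a 30% target, that the stated 10-point precision is wrong, or that the study is underpowered for sensitivity. The documents do not support this. The 30% is a minimum and the 85% an expectation, and planning above a minimum is normal. The 10 points are claimed only at 85%, where they hold. At 85%, and even at a true 60%, 64 impaired patients clear the floor almost surely. What remains is that the article never explains how the two figures relate, and that precision would be poorer (12.8 points) if true sensitivity lay near the floor.

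**Conclusion.** The point holds, mainly for specificity and for the wording of the abstract. The claim that the study is powered has no calculation behind it in this document.

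At the planned specificity of 90%, the chance that the lower 97.5% limit exceeds 90% is 1–2%. About 80% or more requires a true specificity of roughly 93.5% to 94%. These figures assume exactly 10% prevalence (576 normal healers) and the lower-limit rule.

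The number 640 and its stated half-lengths are correct, and sensitivity is not underpowered on the plan's own assumption. The planning pair of 85% and 90% also implies a PPV of 48.6%, short of the 60% aim, so the sample size section has not been brought into line with the stated aims.

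**What to change.** Keep 640 and change the text:

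1. In the abstract, replace the statement that the study is powered to validate the targets with one that it is sized for precision.
2. Say that 30% is the minimum acceptable sensitivity and 85% the expected one, and give the half-length at both: 10.0 and 12.8 points.
3. If specificity above 90% is to be claimed as confirmed, state that the lower 97.5% limit must exceed 90%, name the interval method, and say that 640 gives about 80% power or more only if true specificity is about 93.5–94%. Otherwise report specificity as an estimate with its interval and make no claim of confirmation.
4. Reconcile these figures with the PPV aim of more than 60%, which the planning values do not reach at 10% prevalence.

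The cost is a less favourable published claim. No extra patients are needed. The change should be made before results are known.
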